### **3.8.8.3. Prohibited Concomitant Medications or Therapies**

The use of concomitant medications and non-drug therapies that interfere with the evaluation of the efficacy of IMPs or affect the condition of SLE is prohibited during the trial, mainly including but not limited to the following:

- Other investigational products (biological or non-biological agents);
- Other drugs for the treatment of SLE in addition to the standard of care regimen, such as rituximab or other biological agents for the treatment of SLE, tumour necrosis factor inhibitors, interleukin receptor blockers, etc.;
- Intravenous immunoglobulins;
- Plasma exchange, leukocyte separation;
- Live vaccines or attenuated live vaccines;
- Cyclophosphamide;
- Thalidomide, iguratimod, Chinese herbal medicines and drug products containing Tripterygium wilfordii.

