#### Standard of Care:

All subjects will maintain a stable standard of care regimen for at least 30 days before the first dose of IMP and will continue the standard of care regimen during the trial. The standard of care regimen refers to the use of any of the following (alone or in combination): corticosteroids, antimalarials, NSAIDs, immunosuppressants or immunomodulators [including azathioprine, mycophenolate (including mycophenolate mofetil, mycophenolic sodium), methotrexate, leflunomide, tacrolimus, ciclosporin]. If the subject's condition changes, the standard of care regimen is allowed to be adjusted as needed per the clinical condition, and the reason for adjusting the treatment regimen needs to be recorded.

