### **3.7. Selection of Study Population**

#### **3.7.1. Inclusion Criteria**

A subject will be eligible for inclusion in this study only if all of the following criteria apply:

1. Males or females, aged  $\geq 18$  and  $\leq 65$  years old;
2. Diagnosed with SLE according to the 2019 European League Against Rheumatism (EULAR)/American College of Rheumatology (ACR) classification criteria for SLE (see Appendix 1) based on documented medical history and/or examination results.
3. SELENA-SLEDAI score  $> 0$  and  $\leq 12$  during the screening period;
4. Positive serological findings for autoantibodies during the screening period, defined as: positive antinuclear antibody (ANA) and/or positive anti-ds-DNA antibody as determined based on the reference range of each study site's laboratory; borderline findings will not be accepted;
5. Maintain a stable standard of care regimen for at least 30 days before the first dose of

IMP. Stable standard of care regimen refers to the stable use of any of the following (alone or in combination): corticosteroids, antimalarials, nonsteroidal anti-inflammatory drugs (NSAIDs), immunosuppressants or immunomodulators, such as azathioprine, mycophenolate (including mycophenolate mofetil, mycophenolate sodium), methotrexate, leflunomide, tacrolimus, ciclosporin [Note: Routine dose reduction of corticosteroids  $\leq 20$  mg/d prednisone (or equivalent dose of other corticosteroids) will also be considered as stable therapy];

6. Subjects and their partners agree to use effective contraception during the following time periods (from screening to 4 months after the last dose of IMP for female subjects and their partners, from screening to 6 months after the last dose of IMP for male subjects and their partners) (see Appendix 6);
7. Capable of understanding the nature of the study and voluntarily signing the ICF;
8. Able to communicate well with the investigator and complete all visits according to the protocol requirements.

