### **3.7.2. Exclusion Criteria**

A subject will not be eligible for inclusion in this study if any of the following criteria apply:

1. Renal disorder: Severe lupus nephritis (defined as urine protein  $> 6$  g/24 hours or serum creatinine  $> 2.5$  mg/dL or  $221 \mu\text{mol/L}$ ) within 8 weeks before the first dose of IMP, or active nephritis requiring treatment with drugs prohibited by the protocol, or conditions requiring hemodialysis, or treatment with prednisone  $\geq 100$  mg/d or equivalent glucocorticoids for  $\geq 14$  days;
2. Subjects with central nervous system diseases caused by SLE or non-SLE (including epilepsy, psychosis, organic encephalopathy syndrome, cerebrovascular accident, encephalitis, central nervous system vasculitis) within 8 weeks before the first dose of IMP;
3. The presence of the following laboratory test abnormalities, including but not limited to:
  - a) Subjects with abnormal hepatic function, such as aspartate aminotransferase (AST) or alanine aminotransferase (ALT)  $> 2$  times the upper limit of normal (ULN), total bilirubin  $> 1.5$  times ULN, or

- b) Subjects with abnormal renal function: creatinine (Cr) or urea nitrogen (BUN) > 1.5 times ULN; screening glomerular filtration rate (eGFR)  $\leq 60$  mL/min/1.73 m^2, or
  - c) Subjects with abnormal hematology results: white blood cell count <  $2.5 \times 10^9$ /L, hemoglobin < 85 g/L, platelet count <  $50 \times 10^9$ /L;
4. Subjects with a history of clinically significant diseases that the investigator believes will pose a risk to the subject's safety, or that will affect the safety or efficacy analysis and evaluation if the disease/condition worsens during the study (such as abnormalities of the circulatory system and endocrine system, nervous system diseases, blood system diseases, immune system disorders, mental illness, and unstable metabolic abnormalities), for example: 1) cardiovascular disorder: history of acute myocardial infarction, or unstable angina pectoris, severe arrhythmia (multifocal premature ventricular contractions, ventricular tachycardia, ventricular fibrillation) within 6 months before screening; New York Heart Association (NYHA) Class III-IV; 2) subjects with known moderate or severe persistent asthma within 5 years before screening, or subjects with ongoing inadequately controlled asthma;

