16. Targeted drug therapy: received rituximab within 180 days before the first dose of IMP; received any drug therapy targeting T or B lymphocytes, cytokines, or receptors (e.g., belimumab, telitacicept, abatacept, etc.) within 180 days before the first dose of IMP; received JAK inhibitor therapy within 30 days before the first dose of IMP; or within 5 half-lives after discontinuation of the above drugs (whichever is longer);
17. Received intravenous cyclophosphamide within 180 days before the first dose of IMP or oral cyclophosphamide within 30 days before the first dose of IMP;
18. Used intravenous immunoglobulins (IVIG), prednisone  $\geq 100$  mg/d or equivalent glucocorticoids, or undergone plasmapheresis within 28 days before the first dose of IMP;
19. Used IL-2, thalidomide, Tripterygium wilfordii Hook F, or drug products containing Tripterygium wilfordii Hook F within 28 days before the first dose of IMP;
20. Known allergy to monoclonal antibodies or to excipients of CM313;
21. Patients with depression or tendency for suicide;
22. A history of large alcohol consumption [i.e., more than 14 units of alcohol per week (1 unit = 360 mL of beer or 45 mL of liquor containing 40% alcohol or 150 mL of wine)] or a history of drug abuse within 3 months prior to screening;
23. Female subjects who are pregnant or lactating, or planning to become pregnant or breastfeeding during the study; males whose partners plan to become pregnant during the study;

24. Any reason that, in the opinion of the investigator, contraindicates the subject's participation.

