#### **3.8.8.1. Standard of Care**

The standard of care regimen refers to the use of any of the following (alone or in combination): corticosteroids, antimalarials, NSAIDs, immunosuppressants or immunomodulators [including azathioprine, mycophenolate (including mycophenolate mofetil, mycophenolic sodium), methotrexate, leflunomide, tacrolimus, ciclosporin].

Antimalarials in the standard of care regimen: hydroxychloroquine maximum dose of 400 mg/day. Quinacrine (Atabrine, Mepacrine) maximum dose of 100 mg/day.

The maximum dose of corticosteroids (equivalent to prednisone dose) in the standard of care regimen is 1 mg/kg/day, and maximal daily dose should be no more than 60 mg/day. For subjects with SLE treated with corticosteroids every other day, the average daily dose of corticosteroids is calculated by taking the average of the 2-day dose.

The maximum dose of azathioprine in the standard of care regimen is 200 mg/day. The maximum dose of mycophenolate mofetil (MMF) is 2 g/day. The maximum dose of methotrexate is 25 mg/week. The maximum dose of ciclosporin is 4 mg/kg/day. The maximum dose of tacrolimus is 0.1 mg/kg/day. The maximum dose of leflunomide is 40 mg/day.

If the subject's clinical condition changes, the standard of care regimen is allowed to be adjusted as needed per the clinical condition, and the reason for adjusting the treatment regimen needs to be recorded.

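### Iguratimod is banned during the trial, but no eligibility criterion clearly excludes a current or recent user

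*Protocol*

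**What the plan says.** Section 3.8.8.3 of the protocol lists treatments that may not be used during the trial because they could interfere with the efficacy evaluation or affect SLE itself. One bullet reads "Thalidomide, iguratimod, Chinese herbal medicines and drug products containing Tripterygium wilfordii". Another bars "Other drugs for the treatment of SLE in addition to the standard of care regimen".

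Exclusion 19, worded identically in the synopsis and in section 3.7.2, removes a subject who "Used IL-2, thalidomide, Tripterygium wilfordii Hook F, or drug products containing Tripterygium wilfordii Hook F within 28 days before the first dose of IMP". Iguratimod is not on that list. The ban in 3.8.8.3 is the only place where the protocol names it.

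Background therapy is described in two ways. Inclusion 5 (section 3.7.1) asks for at least 30 days of stable treatment and gives an open list: "immunosuppressants or immunomodulators, such as azathioprine, mycophenolate" and others. Section 3.8.8.1 lists "immunosuppressants or immunomodulators [including azathioprine, mycophenolate (including mycophenolate mofetil, mycophenolic sodium), methotrexate, leflunomide, tacrolimus, ciclosporin" and then sets maximum doses. According to the synopsis, subjects "will continue the standard of care regimen during the trial".

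**The concern.** Three agents are banned by name in one bullet. Two of them must have been stopped at least 28 days before the first dose, and the third has no stated interval. The protocol gives no reason for the difference, so it looks like an omission.

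A site would see iguratimod in the SLE medication history, which covers at least two years, and could decline the subject. The criteria do not require it to. If the subject is randomized, there are two outcomes. Either iguratimod continues and 3.8.8.3 is breached, or it is stopped shortly before Day 1. In the second case the baseline, and the early changes measured from it, may partly reflect withdrawal of a drug that the protocol itself treats as able to disturb the efficacy evaluation.

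**Working it through.** No formula applies, since this is a comparison of the ban with the entry criteria.

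**Step 1. Look-back for each drug named individually in section 3.8.8.3**

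| Drug | Look-back before first dose | Source |
|---|---|---|
| Rituximab | 180 days, or 5 half-lives if longer | Exclusion 16 |
| Cyclophosphamide | 180 days intravenous, 30 days oral | Exclusion 17 |
| Thalidomide | 28 days | Exclusion 19 |
| Tripterygium products | 28 days | Exclusion 19 |
| Iguratimod | none stated | – |

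Several categories on the banned list also have look-backs: live vaccines (exclusion 14), other investigational products (15), and intravenous immunoglobulin and plasmapheresis (18). Iguratimod is the only individually named drug without one.

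**Step 2. Could another criterion cover it?**

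- Exclusion 1 reaches banned drugs only through "active nephritis requiring treatment with drugs prohibited by the protocol". A user without active nephritis is untouched.
- Exclusion 16 covers therapy aimed at T or B lymphocytes, cytokines or receptors. Its examples are belimumab, telitacicept and abatacept. Iguratimod is not named, and the protocol does not describe its mechanism.
- Exclusion 24 is "Any reason that, in the opinion of the investigator, contraindicates" participation. It permits refusal but does not require it.
- The ban in 3.8.8.3 governs conduct during the trial and sets no interval before dosing. Under section 4.1.2, eligibility on Day 1 is verified against the inclusion and exclusion criteria.

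**Step 3. Does the 30-day stability rule in inclusion 5 act as a washout?** That depends on whether iguratimod counts as standard of care.

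- *If it does*, stopping it within 30 days of the first dose is a regimen change and fails inclusion 5, so at least 30 days off drug would be needed. But a subject who stays on it at a stable dose then meets inclusion 5 and is expected to continue a drug that 3.8.8.3 bans by name.
- *If it does not*, no minimum time off drug is stated. A subject stable on hydroxychloroquine, for example, could stop iguratimod the day before Day 1 and meet every explicit criterion.

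The second reading fits the text better. Section 3.8.8.1 names six immunosuppressants or immunomodulators (azathioprine, mycophenolate, methotrexate, leflunomide, tacrolimus and ciclosporin) and sets a maximum dose for each; for mycophenolate the cap is given for mycophenolate mofetil. Iguratimod is neither listed nor capped.

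**Step 4. Minimum time off iguratimod before the first dose**

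| Situation | Days |
|---|---|
| Not standard of care (better reading) | none stated |
| Standard of care, and stopping counts as a change | 30 |
| With iguratimod added to exclusion 19 at 28 days | 28 |

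**Step 5. Weight of one subject.** Each dose level has 8 subjects on CM313 and 2 on placebo (section 8.1). One affected subject is 1/8 = 12.5% of a CM313 group or 1/2 = 50% of a level's placebo subjects. This holds for any single subject; it shows how little averaging there is and says nothing specific to iguratimod.

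**The case against.** The strongest reply is that the two lists were never meant to mirror each other. The banned list is expressly non-exhaustive. Exclusion 19 includes IL-2, which 3.8.8.3 does not name, and leukocyte separation is banned without a look-back. An asymmetry in wording is not in itself a broken rule. That is fair, but leukocyte separation is a procedure, and iguratimod remains the only individually named drug left without an interval.

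A current user is also barred in substance. The ban is explicit, the medication history is taken, and eligibility is checked twice. The protocol also deals with a breach through treatment discontinuation (3.8.7), withdrawal (3.7.4) and the per-protocol set definition (8.2). This largely answers the case of someone who stays on the drug, although those provisions act after randomization. It does not answer the case of someone who stops just before Day 1. If the trial is taken to begin at consent, the ban would cover screening, but 3.8.8.3 does not say when it starts.

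Exclusion 16 is an open category, and whether iguratimod falls within it depends on pharmacology that the protocol does not give. That point stands. It means coverage cannot be ruled out, and equally that a site is not told to apply it.

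Finally, no consequence has been shown, and nothing in the protocol supports 28 days for this particular drug. Both points are accepted, and they set the weight of the concern.

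**Conclusion.** The concern holds: a current or recent iguratimod user is not clearly excluded, although the drug is banned once the trial is under way. This rests on reading iguratimod as outside standard of care and outside exclusion 16. Both readings fit the text, but neither is stated in it.

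The importance is low. The number of subjects affected is unknown and may be zero. The protocol gives no data on how long the drug's effect lasts, so the size of any distortion cannot be judged. Efficacy is exploratory and summarized descriptively, and the primary safety endpoint is little affected. This is a cheap improvement to the eligibility criteria and not a threat to the trial's main conclusions.

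**What to change.** Add iguratimod to exclusion 19 in both the synopsis and section 3.7.2. The existing 28-day look-back would align it with thalidomide and Tripterygium. Whether 28 days is long enough for this drug is for the sponsor's clinicians, who may prefer a longer interval.

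The cost is one word in one criterion, in two places, and at most a few screen failures. A subject who fails for insufficient washout may be re-screened under sections 3.1 and 3.7.3.

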### **3.8.8.4. Permitted Concomitant Medications or Therapies**

If other diseases occur during the study, drugs that do not affect the efficacy of the IMP (such as antibiotics) can be used, but the reasons for medication and medication conditions should be recorded in detail.

If vaccination with the COVID-19 vaccine (limited to inactivated vaccines) is planned during the study, the vaccination time should be  $\geq 7$  days apart from the administration of the IMP.

All medications/therapies other than the IMP, including Chinese herbal medicines and some other non-traditional therapies, are considered concomitant therapies. All concomitant therapies should be recorded in the eCRF, including but not limited to the following information: generic name of the drug, dose level, route of administration, start date, end date, and indication, etc. Any dose adjustments or changes in the treatment regimen of any concomitant therapies should be recorded in the eCRF.

### 3.8.9. Medication Compliance

In the recruitment and screening periods, details about the purpose of this study, the basic information of the IMPs, protocols, study procedures, dosing regimens (e.g., dose, route of administration, etc.), clinical observation, frequency and procedures of and the biological sample collection, potential risks of participating in the study, compensation and reparation, etc. should be introduced to the subjects so as to make the subjects fully informed and participate voluntarily, to improve drug administration compliance. Prior to dosing, the subject number and dose administered should be carefully checked.

The site should record and maintain shipment and receipt records of the IMPs, and the sponsor should be informed immediately of any problems with quality, quantity, or cold chain transportation. The site should accurately record dose preparation information to ensure that all relevant/required information regarding dose preparation and administration is documented in the dose source document and that appropriate dose information is entered into the eCRF. Such information should be provided to the sponsor's authorized monitoring representative during the monitoring visit. After termination of the study, or at the request of the sponsor, the drug administrator must return the remaining IMPs and empty vials to the sponsor.

## 3.9. Endpoints

### 3.9.1. Safety Endpoints

Safety evaluation endpoints include: AEs (including TEAEs, SAEs, TEAEs leading to early withdrawal, etc.), abnormalities in physical examination, vital signs, 12-lead ECG, laboratory tests (including hematology, blood chemistry, urinalysis, and coagulation function), etc.

|                      |                                                                                                                                                                                                                                                                                                                                                                               |
|----------------------|-------------------------------------------------------------------------------------------------------------------------------------------------------------------------------------------------------------------------------------------------------------------------------------------------------------------------------------------------------------------------------|
| Physical Examination | Head and face, eyes, ears, nose and throat, oral cavity, skin, lymph nodes, respiratory system, cardiovascular system, abdomen, genitourinary system (if necessary), musculoskeletal system, nervous system, and mental status.                                                                                                                                               |
| Vital Signs          | Body temperature, pulse, respiration, and blood pressure                                                                                                                                                                                                                                                                                                                      |
| 12-lead ECG          | Heart rate, PR interval, QRS duration, QT interval, and QTcF                                                                                                                                                                                                                                                                                                                  |
| Hematology           | Red blood cells, hemoglobin, white blood cells, hematocrit, platelets, neutrophil count and percentage, lymphocyte count and percentage, monocyte count and percentage                                                                                                                                                                                                        |
| Blood Chemistry      | Glucose, total cholesterol, low density lipoprotein cholesterol, high density lipoprotein cholesterol, alanine aminotransferase, aspartate aminotransferase, total protein, albumin, total bilirubin, direct bilirubin, lactate dehydrogenase, alkaline phosphatase, glutamyl transpeptidase, creatinine, urea/urea nitrogen, uric acid, sodium, potassium, chloride, calcium |
| Urinalysis           | Urine protein, urine glucose, ketones, occult blood, microscopic examination (including red blood cells/HPF, white blood cells/HPF, poikilocytes, casts and                                                                                                                                                                                                                   |

|             |                                                                                                                    |
|-------------|--------------------------------------------------------------------------------------------------------------------|
|             | specific classification), urobilinogen, urine bilirubin, nitrite, urine specific gravity, acidity or alkalinity.   |
| Coagulation | Prothrombin time, activated partial thromboplastin time, thrombin time, fibrinogen, international normalized ratio |

### 3.9.2. Pharmacokinetic Endpoints

PK evaluation endpoints include CM313 blood concentration, PK parameters after the first dose [including  $T_{max}$ ,  $C_{max}$ ,  $AUC_{tau}$ ,  $AUC_{0-t}$ , etc.], PK parameters after the last dose [including  $T_{max}$ ,  $C_{max}$ ,  $AUC_{tau}$ ,  $AUC_{0-t}$ ,  $AUC_{0-\infty}$ ,  $T_{1/2z}$ , CL,  $V_z$ ,  $MRT_{0-t}$ ,  $R_{ac}$ , etc.].

### 3.9.3. Pharmacodynamic Endpoints

PD evaluation endpoints include: immunophenotyping, including T lymphocytes (CD3/CD4/CD8/CD38), B lymphocytes (CD19/CD138/CD27/CD38), pDC cells (CD123/BDCA2/CD38), and NK cells (CD56/CD16/CD38); type I IFN-related gene expression.

